#### Evaluation of the models

All the predictors presented along with the outcomes were selected because they have been considered potentially related to that particular outcome and could help to predict the observed variability. Harrell’s method [23] will be applied for variable reduction. First, the model will be run including only one key predictor variable. Then, in an iterative process each predictor will be included along with the key predictor cited above in a model. If in any of these steps a predictor changes the parameter estimate by more than 10%, it will be retained in the model. Finally, the definitive multivariable model will consist of the key predictor chosen and all the variables that changed the parameter estimate by more than 10%. The key predictor for the outcomes understanding, and accessibility of information will be the arm to which the participants were randomly allocated. For the outcome participants’ preference for a table, the order in which the tables were shown will be the key predictor.

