### Overview of the design

We will conduct a parallel-armed, non-inferiority randomized trial comparing a new alternative format of SoF tables with current format. We will contact systematic review users by Email and ask them to fill a questionnaire developed using the 'Survey Monkey' online system. The data collection form will include questions about baseline information (demographic characteristics, background, familiarity with systematic reviews and the GRADE system, and so on). Then, participants will be randomly assigned to one of two SoF tables, either the one in the alternative format or the one with the current format (See Figure 1). Randomization will be stratified according to participants’ background (health professional, guideline developer, researcher). They will be asked to answer questions to determine understanding, accessibility of information, and satisfaction with the table format to which they were allocated. Finally, we will show them the other table format to which they were not initially allocated in order to test their preference for either one.

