The proportion of participants correctly answering questions about understanding in similar randomized controlled trials that tested the current SoF table format was between 80 to 87% [17,18], and we expect, at least, the same percentage in the group of participants randomized to the alternative format of SoF table. A non-inferiority margin of 10% was set, and an allocation of 1:1 participants will be used. If there is truly no difference between the current and the alternative table format, then 280 participants are required to be 80% sure that the upper limit of a 1-sided 95% confidence interval (CI) will exclude a difference in favor of the current SoF table format of more than 10%. Assuming that 10% of participants would not complete the questionnaire, we aim to recruit a total of 308 participants. Linear and logistic regressions will be used as a method of analysis. According to Hsieh *et al*. [22], when more than one covariate is included in the model, a variance inflation factor should be added to the typical univariate analysis to obtain the required sample size. Equation 3 represents the variance inflation factor cited, where *b*_1_ represents the maximum likelihood estimate of *β*_1,_ var_p_(*b*_1_) corresponds to the variance of *b*_1_ that it is approximated from a one parameter model to a multivariate case when multiplied by 1/(1 - ρ^2^_1.23….p_), where ρ_1.23….p_ is the multiple correlation coefficient associating *X*_1_ with *X*_2_,…*X*_p_.

From unvariate to multivariate regression model sample size estimation:3$$ \mathrm{v}\mathrm{a}{\mathrm{r}}_{\mathrm{p}}\left({b}_1\right) = \mathrm{v}\mathrm{a}{\mathrm{r}}_1\left({\mathrm{b}}_1\right)/\left(1\hbox{-} {\uprho^2}_{1.23\dots .\mathrm{p}}\right) $$

Since this is a clinical trial in which participants will be allocated to the study arms randomly, it can be assumed that no correlation exists between being assigned to a particular arm and any of the predictors considered for analysis. Then, the value of ρ in the current study is zero, and the estimated sample size is the one described above.

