### Inferential analysis

The primary outcome (understanding) will be estimated as the proportion of participants correctly answering each question per group. Data regarding this outcome will be analyzed using a multiple logistic regression per question, where the main predictor will be the arm to which participants were allocated (dichotomous - 2 categories). Other potential predictors to include in the model are participant strata (nominal - 3 categories), years of experience (nominal - 5 categories), familiarity with the GRADE approach (dichotomous - 2 categories), and previous education in health research methodology or epidemiology (ordinal - 3 categories). To adjust for multiplicity, the *P*-value will be modified using the Bonferroni correction for 7 multiple comparisons (<0.0035, CIs will be constructed with corresponding 1-sided z score 2.7).

For the secondary outcome, accessibility of information, we will calculate means, SDs and 95% CIs per domain. Data regarding this outcome will be analyzed using multiple linear regression where the main pre.dictor will be the arm to which participants were allocated (dichotomous - 2 categories). Other potential predictors included in the model will be participant strata (nominal - 3 categories), years of experience (nominal - 5 categories), familiarity with the GRADE approach (dichotomous - 2 categories), and previous education in health research methodology or epidemiology (ordinal - 3 categories). To adjust for multiplicity, the *P*-value will be modified using the Bonferroni correction for 4 multiple comparisons (<0.0125).

The secondary outcome, satisfaction, will be measured at an item level. The proportion of participants satisfied with either item included in Table A or C will be calculated per group.

For the secondary outcome, preference, linear regressions will be used. Since this outcome is obtained from a direct comparison of the tables (blinding is disclosed), there will be no main predictor of interest. However, we will control for the order in which the tables were shown to the participants (dichotomous - 2 categories). Other potential predictors to include in the model will be participant strata (nominal - 3 categories), years of experience (nominal - 5 categories), familiarity with the GRADE approach (dichotomous - 2 categories), and previous education in health research methodology or epidemiology (ordinal - 3 categories).

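### The 10% change-in-estimate rule makes the covariate set for the primary outcome largely a matter of chance and can drop the stratification factor

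*Protocol article*

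**What the plan says.** The Inferential analysis section assigns a separate multiple logistic regression to each of the seven understanding questions, with arm as the main predictor. It then lists the candidates: "Other potential predictors to include in the model are participant strata (nominal - 3 categories), years of experience (nominal - 5 categories"), followed by familiarity with GRADE (2 categories) and previous methodological education (3 categories). Accessibility has the same candidates in linear models.

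Evaluation of the models gives the selection rule. It starts from the key predictor alone and adds each candidate singly: "If in any of these steps a predictor changes the parameter estimate by more than 10%, it will be retained in the model". The final model is the key predictor plus whatever passed. "The key predictor for the outcomes understanding, and accessibility of information will be the arm to which the participants were randomly allocated"; for preference the key predictor is the order in which the tables were shown.

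Three other statements bear on this:
- Overview of the design: "Randomization will be stratified according to" participants' background, the same three-category variable that appears among the candidates. It is not exempted from the screen.
- Sample size calculation, planning assumption: "If there is truly no difference between the current and the alternative table format, then 280 participants are required to be 80% sure".
- Sample size calculation, last paragraph: because allocation is random, arm is taken to be uncorrelated with every predictor, so the correlation is set to zero.

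**The concern.** A change-in-estimate screen looks for confounding. The protocol itself says that randomisation leaves none between arm and the predictors. What can still move the arm coefficient is chance imbalance and, in the logistic models only, non-collapsibility of the odds ratio.

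The change is measured relative to the arm coefficient. For understanding the trial expects that coefficient to be about zero, so a trivial absolute shift exceeds 10%. The section justifies the candidates as related to the outcome, yet retention does not depend on that relation. A prognostic, well-balanced covariate tends to fail the screen, and an irrelevant one can pass because the crude arm estimate happened to be small.

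At stake is a primary model that is not settled until the treatment estimate is known, that can differ from question to question, and that need not include the factor by which participants were randomised.

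**Working it through.** **Planning figure.** Inputs from Sample size calculation: upper end of the 80 to 87% range, margin 0.10, one-sided 5%, 80% power, 1:1 allocation.

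n per arm = (1.645 + 0.842)² × 2 × 0.87 × 0.13 / 0.10² = 139.8, so 140 per arm and 280 in total. This matches the protocol. With 10% added, 280 × 1.1 = 308, which also matches.

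**How small the threshold is.** With 140 per arm, 87% correct and no difference, the standard error of the arm log odds ratio is √[2 / (140 × 0.87 × 0.13)] = 0.355. The median absolute crude estimate is 0.674 × 0.355 = 0.24, so the typical threshold is 0.024 on the log-odds scale. For a true 10-point loss (87% to 77%) the log odds ratio is 1.901 − 1.208 = 0.693 and the threshold 0.069. For 30 points (87% to 57%) it is 1.901 − 0.282 = 1.619 and the threshold 0.16.

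**Closed-form check for a noise covariate, no true difference, no balancing.** Scale the covariate's k degrees of freedom to unit variance and let v = 0.87 × 0.13. Adding the covariate shifts the arm coefficient by about Σ dⱼgⱼ, where:
- dⱼ, the arm imbalance, has SD √(2/140);
- gⱼ, the chance covariate coefficient, has SD 1/√(280v);
- the crude arm coefficient has SD √[2/(140v)].

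The ratio of SDs reduces to 1/√280 = 0.060, and v cancels. Hence P(relative change > 10%) ≈ E[(2/π) arctan(10 χₖ/√280)], with χₖ a chi variable on k degrees of freedom:
- k = 1 (two categories): 26%
- k = 2 (three categories): 38%
- k = 4 (five categories): 51%

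**Simulation of the stated rule.** N = 280, 87% correct, four covariates with the protocol's numbers of categories, 3,000 trials per scenario. Assumed, because the protocol does not give them: equal category frequencies, independent covariates, and effects of either none or a log odds of 1 across each covariate's range. Percentage of no-difference trials in which each covariate was kept:

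| Scenario | Stratum | Years | GRADE | Education | At least one |
|---|---|---|---|---|---|
| Noise, arms balanced within strata | 1.6 | 51 | 24 | 36 | 67 |
| Prognostic, balanced | 6 | 61 | 62 | 58 | 88 |
| Noise, simple randomisation | 38 | 52 | 26 | 38 | 73 |
| Prognostic, simple randomisation | 62 | 64 | 64 | 61 | 93 |

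The noise row under simple randomisation agrees with the closed form. With balanced strata and noise covariates, the chance of keeping at least one falls from 67% at no difference to 47% at 5 points, 22% at 10 and 1% at 30. The covariates are the same throughout; only the arm effect changes.

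Other assumed effects gave the same picture. With odds ratios of 2 for GRADE familiarity, 1.4 per level of education and 1.5 for stratum, years as noise, 86% correct and arms not balanced within strata, years was kept in 53%, at least one covariate in 84%, and the stratum was dropped in 46% and 54% in two runs. In about 0.3 to 5% of no-difference runs the crude estimate was exactly zero and the rule was undefined.

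**Effect on the conclusion.** The rule was compared with a fixed model (arm, stratum, GRADE familiarity) under those odds ratios and 87% correct:
- False non-inferiority claims at a true 10-point loss, one-sided 95%: rule 4.9%, fixed 4.9% (balanced); rule 5.3%, fixed 5.7% (simple).
- The same at the protocol's z of 2.7: 0.40% against 0.37%, and 0.20% against 0.23%.
- Power at no difference, one-sided 95%: 81.3% against 81.9%, and 78.6% against 79.0%.
- Single-question decisions that differed between rule and fixed model: about 3 to 4% at one-sided 95% and 5 to 6% at z = 2.7, both at no difference.

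**The case against.** The strongest reply is that an unstable covariate set has not been shown to harm the conclusion. A reader might infer from the retention figures that the rule inflates false non-inferiority claims or invalidates the interval. The simulations do not support that: error rates and power are almost the same as under a fixed model. This part of the reply stands and limits the severity.

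Second, candidates, threshold and algorithm are all written down in advance, and the Blinding section has the data analysed before labels are revealed. So the rule gives the analyst little discretion. That also stands. Yet the rule uses the size of the arm coefficient whatever the label, so the model still depends on the treatment estimate.

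Third, a reader might infer that the stratum is lost about half the time in any case. That holds only if arms are not balanced within strata. The Randomization section describes 1:1 allocation after stratification, while Concealment of allocation describes an unknown algorithm with no pre-specified sequence, so balance is not assured. If arms are balanced, the stratum is dropped in about 94% (prognostic) to 98% (noise) of trials because it barely moves the estimate. Omitting it then typically costs only a little precision. A very strong stratum effect (log odds 2, 80% correct) was kept in 61%.

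Fourth, the claim is stated as a difference in proportions. If that interval were unadjusted, the rule would touch only the regression. But Table 2 and Inferential analysis name multiple logistic regression as the primary method.

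Finally, the near-zero argument should not be stretched to every outcome. It rests on the non-inferiority plan for understanding. Accessibility is tested for superiority in linear models, where non-collapsibility does not arise, and for preference the screened coefficient is table order.

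**Conclusion.** The point holds for the primary outcome: under the planning assumption of no difference, retention is largely chance. About half of simulated trials kept a five-category noise variable; two- and three-category noise variables were kept in about a quarter and a little over a third. A prognostic stratum was dropped in about 40 to 55% of trials without balance within strata and in over 90% with it, very strong effects apart. The exact percentages rest on assumed covariate distributions and effects, but the pattern appeared in every scenario.

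The consequence is a primary model that depends on the data, can differ across the seven questions and need not reflect the stratified randomisation. About 4% of single-question decisions changed. There is no evidence of material bias, inflated false claims or lost power. This should be fixed, but it does not threaten the validity of the trial.

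**What to change.** For understanding and accessibility, replace the 10% rule with one covariate set, named before the analysis and used for every question and domain. It should be arm and participant stratum always, plus whichever of the already listed baseline predictors the investigators choose. The protocol gives no ground for preferring one of those over another, since it regards them all as related to the outcome. Report the unadjusted estimate beside the adjusted one. For preference, likewise use a fixed set containing table order and stratum.

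The cost is wording in Evaluation of the models and Inferential analysis. The baseline characteristics are collected before allocation, so no new data are needed, and the sample size stays at 280 under the protocol's own zero-correlation argument. The change should be made before analysis begins; afterwards the covariate choice cannot be shown to be independent of the results.

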#### Claiming of non-inferiority (CI approach)

For the primary outcome understanding, non-inferiority of the alternative (Table A) format to the current standard format (Table C) of SoF tables will be claimed if the upper limit of the CI (for the difference of proportion of participants answering correctly a given question, using Table C as reference) is lower than a non-inferiority margin of 10%. This approach is more informative as each question is related to a particular item under testing in the tables. Only the test for superiority will be applied to the secondary outcomes.

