**Methods/Design:**

We will conduct a non-inferiority parallel-armed randomized controlled trial to determine whether an alternative format to present risks and display Summary-of-Findings tables is not inferior compared to the current standard format. We will measure participant understanding, accessibility of the information, satisfaction, and preference for both formats. We will invite systematic review users to participate (that is clinicians, guideline developers, and researchers). The data collection process will be undertaken using the online 'Survey Monkey' system. For the primary outcome understanding, non-inferiority of the alternative format (Table A) to the current standard format (Table C) of Summary-of-Findings tables will be claimed if the upper limit of a 1-sided 95% confidence interval (for the difference of proportion of participants answering correctly a given question) excluded a difference in favor of the current format of more than 10%.

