SoF tables have undergone deliberate development. The current format and content of SoF tables are based on user-testing studies, stakeholder feedback, and two randomized controlled trials [15-17]. These studies showed that SoF tables (incorporated in systematic reviews) significantly improved understanding (93% versus 44% (*P* = 0.003)) and the ability to find critical information (68% versus 40% (*P* = 0.021)) compared to those without SoF tables that report results only in a narrative way [17]. In another randomized trial, it was found that formatting modification of GRADE evidence profiles can increase the comprehension of key findings ranging between 5 to 47% [18].

Since 2004, The Cochrane Collaboration has been intensively working on the implementation of SoF tables in their reviews. By 2014, more than 600 SoF tables had been published across review groups (Langendam et al: Improving GRADE evidence tables: A systematic survey of explanatory footnotes and judgments in Summary of Findings Tables and Evidence Profiles shows more guidance is needed, manuscript in preparation). However, it has been noticed that the current standard format may need to be adapted depending on specific review characteristics. For example, the current SoF table format does not provide specific guidance for scenarios such as the narrative reporting of results when a meta-analysis was not undertaken nor alternative formats of presenting continuous and dichotomous outcomes. The inclusion of alternative presentations of risks in SoF tables included in systematic reviews would allow authors to choose from a variety of scientifically tested items that can be used to fit into the users’ needs.

Considering the above, the aim of this trial will be to determine whether new alternative SoF table format is not inferior compared to current standard format. Inferiority will be assessed by: understanding; perceived accessibility; satisfaction; and preference by health care professionals, guideline developers, and researchers that use and/or develop systematic reviews.

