#### Primary outcome

##### Understanding

It is defined as the correct comprehension of key findings. We will frame seven multiple-choice questions about key concepts in the table with five response alternatives for each question and only one correct answer. We will compare the proportion of correct answers between groups per question. A 10% difference was defined as the minimal important difference between groups.

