## Discussion

This study represents an effort to provide systematic reviewers with additional options to display review results using SoF tables. Since the current format of SoF table has shown to improve understanding and facilitate the rapid retrieval of key findings, with an average of 90 seconds compared to the full text review [17], this time, we plan to conduct a non-inferiority trial with the aim to test an alternative format that can perform at least as effectively as the current one (comparison at a table level). In this way, review authors will have a variety of methods to present risks and more flexibility to choose the most appropriate table features to display (these being optional columns, risks expressions, complementary methods to display continuous outcomes, and so on).

The current trial has several strengths. First, it utilizes feedback and comments from a broad audience of GRADE users with different interests. This feedback informed a series of iterative user-testing rounds to examine the potential usefulness of several alternative formats for SoF tables. Second, it builds upon previous randomized controlled trials comparing the validated current standard format with the new alternative format proposed. Third, following methodological suggestions provided by Akl *et al*.[6] for further trials conducted in the same field, we designed a methodologically sound non-inferiority parallel-armed randomized controlled trial. Fourth, it will include participants from different backgrounds, settings (these being clinicians, guideline developers, and researchers), and different languages, which increases the generalizability of the findings. Fifth, this trial follows the recommendations for reporting provided by the CONSORT group in its extension for reporting of non-inferiority and equivalence randomized trials [19].

This study also has some limitations. First, since the data collection is conducted using an online system, there will be limited control over the environment in which the questionnaire is completed (that is whether it is completed by the same person that the link was sent to, whether the participant used additional information while answering the questions that measures the outcomes, and so on). Second, multiplicity and the corresponding adjustments may influence the precision of the CIs, a situation that may facilitate to find inconclusive results.

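### The non-inferiority claim is worded for the Table A format but tested on a single question, and no rule links the seven question-level verdicts to the stated table-level aim

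*Protocol article*

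**What the plan says.** All places are in the protocol article.

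- **Object of the claim.** Under Claiming of non-inferiority (CI approach): "non-inferiority of the alternative (Table A) format to the current standard format (Table C) of SoF tables will be claimed if the upper limit". This limit belongs to a confidence interval and has to lie below the 10% margin.
- **Criterion.** The interval in that sentence is the one "for the difference of proportion of participants answering correctly a given question, using Table C as reference". The abstract (Methods/Design) gives the same rule, again "for the difference of proportion of participants answering correctly a given question".
- **Number of questions.** Under Understanding: "We will frame seven multiple-choice questions about key concepts in the table". Inferential analysis fits one logistic model per question and applies a Bonferroni correction for seven comparisons (P < 0.0035, one-sided z = 2.7).
- **Reason given for working by question.** "This approach is more informative as each question is related to a particular item under testing in the tables".
- **Level of the aim.** The last paragraph of the Background asks whether the new format is not inferior to the current one. The Discussion describes the purpose as to test "an alternative format that can perform at least as effectively as the current one (comparison at a table level").
- **Outcomes named in the aim.** The Background adds: "Inferiority will be assessed by: understanding; perceived accessibility; satisfaction; and preference". The section on claiming non-inferiority allows only superiority tests for the secondary outcomes, which are the last three of these four.

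The article does not say whether one, most or all seven questions must meet the margin, and it defines no composite score.

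**The concern.** The conclusion and the criterion sit at different levels. The claim is about a table format, the test is about one question, and no rule connects them. The section concerned is the protocol's own decision rule, so the problem lies in what is written rather than in detail left to an analysis plan.

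Seven intervals can easily give mixed verdicts. The authors would then have to decide, after seeing the results, whether the format is non-inferior. The choice matters, because with the same data an any-question reading and an all-questions reading can give opposite conclusions.

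Bonferroni does not settle this. It limits false question-level claims. It does not stop a true pass on one question from being reported as non-inferiority of the table. If all seven questions had to pass, no alpha split would be needed and the correction would only cost power.

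The list of four outcomes adds a second mismatch. A superiority test that does not reach significance cannot show non-inferiority, and the article gives no margin for accessibility, satisfaction or preference.

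**Working it through.** **Inputs from the protocol article.** From Sample size calculation: 280 evaluable participants, 1:1 (140 per arm); margin 0.10; one-sided 5%; power 80%; 80 to 87% correct under Table C; no true difference. From Inferential analysis: z = 2.7 per question. From Understanding: seven questions.

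**Assumptions of this check.** Unpooled Wald limit for the difference C minus A, without covariates. Questions are independent unless a correlation is stated. The deficits of 10 and 15 points and the correlations of 0.3 and 0.6 are not in the documents.

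**1. The stated sample size.** n per arm = (1.645 + 0.842)² × 2p(1 − p) / 0.10².
- p = 0.87: 6.18 × 0.2262 / 0.01 ≈ 139.8, so 140 per arm and 280 in total. This matches the protocol.
- p = 0.80: 6.18 × 0.32 / 0.01 ≈ 197.8, so 198 per arm and 396 in total.

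The 280 therefore covers one question at unadjusted alpha, at the upper end of the stated range.

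**2. Chance of a pass on one question when the tables are equal.** SE = √(2p(1 − p)/140); power = Φ(0.10/SE − z).

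| Correct in both arms | SE | z = 2.7 | z = 1.645 |
|---|---|---|---|
| 87% | 0.0402 | 42% | 80% |
| 80% | 0.0478 | 27% | 67% |

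Exact binomial enumeration at z = 2.7 gives 43.2% and 27.5%.

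**3. Literal reading: any one question suffices.** Table A is equal on one question and exactly 10 points worse on six. By exact enumeration at 87%, the equal question passes with probability 0.432 and each inferior one with 0.0040.

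P(at least one pass) = 1 − (1 − 0.432) × (1 − 0.0040)⁶ = 1 − 0.568 × 0.976 ≈ 0.445.

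At 80% correct the result is 0.291. With the six questions 15 points worse, the results are 0.432 and 0.276. Nearly all of the 44.5% is the 43.2% chance of a correct pass on the equal question.

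**4. What Bonferroni controls.** With all seven questions exactly at the margin and one-sided alpha 0.0035 each, P(any false question-level pass) = 1 − (1 − 0.0035)⁷ ≈ 2.4%. Question-level error is under control.

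**5. All seven must pass, tables truly equal, 280 participants.**

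| Correlation between questions | z = 1.645, 87% | z = 1.645, 80% | z = 2.7, 87% |
|---|---|---|---|
| 0 | 0.80⁷ ≈ 21% | 0.6725⁷ ≈ 6% | 0.4172⁷ ≈ 0.2% |
| 0.3 (simulated) | 36% | 18% | 3.5% |
| 0.6 (simulated) | 50% | 32% | 11% |
| 1 (upper bound) | 80% | 67% | 42% |

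Under independence, 80% joint power at one-sided 5% would need 558 evaluable participants at 87% correct and 788 at 80%.

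**The case against.** The strongest case on the other side is that the plan means seven separate verdicts. It compares proportions per question, fits a model per question, corrects for seven comparisons and ties each question to an item. Bonferroni is the natural correction for that. On this reading a pass on one question says nothing about the other six. The Discussion's reference to a table level may mean only that whole tables are randomised, in contrast with satisfaction, which is measured by item. Its declared purpose, more choice of table features for review authors, is served by answers per question.

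Much of this stands. A reader might infer that the plan would declare Table A non-inferior while it is inferior on six of seven questions, or that its error rate is uncontrolled. The documents do not support either. Nowhere do they say that one question suffices for the table, and the 45% becomes an error rate only if that is assumed first. As a set of question-level claims, the error is about 2.4% in the case worked above. Independence is also a simplification, since the same participant answers all seven questions from one table.

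The objection does not remove the mismatch. The claim sentence names the format, the Background states the aim for the format, and on the charitable reading nothing decides that aim. The limitation on multiplicity in the Discussion concerns the precision of intervals and does not fill the gap.

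**Conclusion.** The point holds as a mismatch between claim and criterion. Either the wording allows a format claim to rest on one question, or the claims are question-level and the table-level aim has no decision rule. The protocol article does not say which.

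The 45% (29% at 80% correct) rests on independent questions, 140 per arm and the assumed pattern of deficits. It marks the outer limit of the literal wording and is not a forecast. Nor does the text compel an all-seven rule. That is one possible table-level rule, and at 280 participants it would be weak.

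The mismatch on outcomes is a separate, smaller inconsistency. It needs no arithmetic and does not bear on the question-to-table gap.

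**What to change.** 1. In the abstract and in Claiming of non-inferiority, word the claim as *Table A is non-inferior to Table C on question k*, at the adjusted level. Add that passes on some questions do not establish non-inferiority of the table as a whole.
2. If a table-level claim is wanted, prespecify its rule before results are seen; the article reports that recruitment is under way. One option is that all seven questions pass, each at unadjusted one-sided 5%. Another is a single composite score as the primary measure. If the all-seven rule is chosen, state its power as tabulated above.
3. In the Background, limit the non-inferiority aim to understanding, and describe accessibility, satisfaction and preference as outcomes tested for superiority.

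**Cost.** Items 1 and 3 are changes of wording, and the price is that the trial can conclude less about the table as a whole. Item 2 is not free: at 280 participants an all-seven claim would probably be missed even if the formats were equal, unless the questions are strongly correlated or the sample is enlarged.
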